### Outcome Measures

We aim to verify the efficacy of an educational intervention program to improve the hygienic conditions and the composition of the menu offered in school cafeterias in the state of Rio Grande do Sul, Brazil. The efficacy of the intervention will consider 2 primary outcomes: (1) composition of the menu offered (percentages of fresh, processed, and ultraprocessed foods) and (2) assessment of hygienic conditions concerning good practices in handling food. The secondary outcome will be a score calculated according to the level of processing of food sold. These variables will be collected at baseline and immediately after the intervention.

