#### Primary Outcomes

The assessment of the impact of the intervention on the composition of the menu offered in school cafeterias will be based on similar Australian studies [25,54]. The assessment of the school cafeteria menu composition will be determined by counting all items sold and the percentages of food classified according to the level of industrial processing proposed by the Food Guide for the Brazilian Population [51] and Monteiro et al [55]. A modified version of these references was used for this research. Group 1 (F*fresh*) includes fresh foods, minimally processed and culinary preparations without the addition of culinary ingredients (salt, sugar, oils, fats, or other ingredients). Group 2 (F*process*) includes processed foods and culinary preparations with culinary ingredients. Group 3 (F*ultra*) includes ultraprocessed foods. The culinary ingredients group proposed by Brazil [31] was excluded from the classification because the cafeterias do not sell these foods in isolation. Two properly trained dietitians will carry out this assessment using pen and paper. In case of divergence, a third dietitian will be consulted.

Good practices in food handling are a set of procedures that food services implement to ensure food quality to the consumer, minimizing possible harm to health, especially that caused by foodborne diseases. In this sense, there is a need to assess and classify the food sold according to the characteristics that include the amount of microbial and chemical contamination [56]. To collect data regarding hygienic conditions, we will use an instrument that has been validated by the National Health Surveillance Agency [57], which is based on Brazilian legislation, Regulatory Ordinance 817, published on May 10, 2013, by the Ministry of Health [56]. This legislation is composed of 51 items from 9 categories: water supply; building structure; cleaning of facilities, equipment, furniture, and utensils; control of vectors and urban pests; food handlers; raw material, ingredients, and packaging; food preparation; storage, transport, and display of prepared food; and liability, documentation, and registration.

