#### Secondary Outcome

To assess the impact of the intervention on the food sold in the cafeteria, we have prepared a score that can be calculated based on the frequency of food available for sale and its classification according to the level of industrial processing proposed by Brazil [51] and Monteiro et al [55]. This score was developed due to the lack of a standard method for analyzing food in the school environment [59] and was also based on similar Australian studies [25,26]. Therefore, in addition to evaluating the composition of the menu offered in primary outcomes, we also chose to develop an equation that uses the frequency of each type of food but makes these variables continuous for a secondary outcome.

After data collection, all types of food and drinks sold in the cafeterias will be classified according to their level of processing. In the second stage, for each cafeteria, the frequency of items available in each category will be counted, multiplied by the standardized weight for the Group of fresh foods, Group of processed foods, and Group of ultraprocessed foods, which are +1, 0, and -1, respectively, as they are healthy, neutral, and unhealthy, respectively.

Equation (1) is used to calculate the score of the cafeteria for the level of food processing, where F*fresh* = frequency of fresh food items; F*process* = frequency of processed foods; F*ultra* = frequency of ultraprocessed foods; n = total number of items sold in the cafeteria, achieved by multiplying the frequency of food in each category by its corresponding weight, added to the values and dividing by the total number of items sold in the cafeteria. The score formula 50R + 50 is used to obtain scores for each establishment.

The score can vary on a scale of 0 to 100 points, where 50 is the midpoint. Thus, a cafeteria that offers healthy (fresh) and unhealthy (ultraprocessed) food in equal quantities will receive an average score of 50 points and will be considered a neutral cafeteria. Cafeterias that reach a score below 50 points have a greater predominance of ultraprocessed foods (ie, a greater offering of unhealthy foods). In summary, higher scores reflect better food quality in the school cafeterias.

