### Statistical Analysis

We will consider the 2 primary outcomes and the secondary outcome: composition of the menu offered (ordinal categorical data), assessment of hygienic conditions concerning good practices in handling food (continuous variables), and the score for the level of processing of food sold (continuous variables). The baseline characteristics of the school and the cafeteria will be presented in conventional descriptive statistics. Continuous variables will be presented as means and standard deviations for symmetric data or medians and interquartile ranges for asymmetric data, while categorical variables will be presented as frequencies and percentages. All outcomes will be analyzed as intention-to-treat and per-protocol. The intention-to-treat analysis will include all participants according to their original group assignment, regardless of what happened later. The per-protocol analysis will consider only those participants who comply with the protocol in terms of eligibility, interventions, and evaluation of results [38]. Unadjusted and adjusted estimates allowing for the potential confounding effects of all minimization factors will be presented for primary and secondary endpoints. Multiple imputation will be used to deal with missing data [60].

For the analysis of continuous data (hygienic conditions and level of processing of food sold), analysis of covariance or a generalized linear model with an appropriate link function will be used, depending on the data characteristics. The outcomes will be assessed by comparing the mean changes (delta) between baseline and follow-up values between the groups, adjusting for the baseline value of the outcome. For the analysis of ordinal categorical data (menu composition and percentages of each type of food), we will use an ordinal logistic regression model to assess between-group differences at follow-up, adjusting for the baseline value of the outcome. All data will be analyzed using the statistical software SPSS 26.0 (IBM Corp, Armonk, NY) and R Software 3.5.0 (R Development Core Team). The statistical level of significance considered will be *P*<.05 for a confidence interval of 95%.

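### Menu composition, a primary outcome defined as three percentages per cafeteria, is labelled ordinal categorical and given an ordinal logistic regression with no ordered response defined

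*Protocol article*

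**What the plan says.** - **Definition.** Outcome Measures lists the first primary outcome as "composition of the menu offered (percentages of fresh, processed, and ultraprocessed foods"). Primary Outcomes says it is obtained by "counting all items sold and the percentages of food classified according to the level of industrial processing". Randomization and Allocation makes the school with a cafeteria the randomized unit.
- **Data type and model.** Statistical Analysis lists the same outcome as "composition of the menu offered (ordinal categorical data") and continues: "For the analysis of ordinal categorical data (menu composition and percentages of each type of food), we will use an ordinal logistic regression model". The model is "to assess between-group differences at follow-up, adjusting for the baseline value of the outcome". The abstract also assigns ordinal logistic regression to ordinal data.
- **Secondary score.** A 0 to 100 score is built from the same item frequencies. The protocol says the equation "uses the frequency of each type of food but makes these variables continuous for a secondary outcome". It is analysed by analysis of covariance or a generalized linear model.
- **Sample size.** Sampling bases 54 schools (27 per arm) on the primary outcomes, with 5% significance, 90% power and d = 0.90.

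**The concern.** Each randomized unit supplies three numeric values, of which two are free because they sum to 100. An ordinal logistic model needs one response with ordered levels, and the article never says what that response is. The analyst must therefore invent one:

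1. cut or rank each percentage into ordered levels, with unstated cut-points and three dependent odds ratios for one outcome; or
2. treat each food item as an observation ordered fresh, processed, ultraprocessed. The unit of analysis is then no longer the randomized unit, and the stated baseline adjustment has no meaning for an item.

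These choices have different error rates and answer different questions, and one of the two primary conclusions depends on them. The Results section says that data are collected and analysis is under way, so an undefined response leaves room for a choice made with results in view.

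**Working it through.** **Step 1. Reproduce the sample size.** Inputs from Sampling: d = 0.90, alpha 5% (two-sided assumed, as sidedness is not stated), power 90%, 27 per arm. For a two-sample t-test, the noncentrality is 0.90 × √(27/2) = 3.31 with 52 degrees of freedom, and the power is 0.9006. The stated 27 per arm is thus reproduced by a comparison of means, before any allowance for loss. No odds ratio or category distribution enters. (How the 10% loss was handled is a separate question.)

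**Step 2. Is the outcome ordinal at cafeteria level?** The documents give no item counts. Assuming 15 to 49 items per cafeteria and average shares of 15/35/50%, simulated sets of 54 cafeterias gave about 43 to 48 distinct values per percentage. That is close to continuous, not a short ordered scale.

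**Step 3. Compare with the secondary score.** From the weights +1, 0 and -1, R = (fresh - ultraprocessed)/n, so

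50R + 50 = 50 + 0.5 × (%fresh - %ultraprocessed).

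Example 20/30/50: R = -0.30, and 50 × (-0.30) + 50 = 35; also 50 + 0.5 × (20 - 50) = 35. The plan therefore treats the percentages as ordinal and an exact linear function of them as continuous.

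**Step 4. Percentages cut into levels.** Simulations of 54 schools with an assumed baseline correlation of 0.5:

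| Analysis | Power, d = 0.5 | Power, d = 0.9 |
|---|---|---|
| Ordinal, tertiles (300 runs) | 48% | 90% |
| ANCOVA, same runs | 56% | 96% |
| Ordinal, 10 / 18 levels (400 runs) | 56% / 58% | 97% / 97% |
| ANCOVA, same runs | 58% | 96% |

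A further tertile run (600 simulations) gave 41–44% against 55% at d = 0.5, and 90% against 97% at d = 0.9. The loss comes from coarse cutting, not from ordinal regression itself. Type I error with 10 or 18 levels was 7%, against 5% for ANCOVA, with a simulation error of about 1.3 points.

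**Step 5. Items as the unit.** With m items per cafeteria, the design effect is 1 + (m - 1) × ICC. If clustering is ignored, the true type I error at nominal 5% is 2 × (1 - Φ(1.96/√DE)). Both m and ICC are assumptions.

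| m | ICC | DE | Type I error |
|---|---|---|---|
| 20 | 0.01 | 1.19 | 7% |
| 40 | 0.05 | 2.95 | 25% |
| 60 | 0.10 | 6.90 | 46% |

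A direct simulation of the item-level test (27 cafeterias per arm, no effect) agrees: at ICC 0.05 it gave 15.6%, 20.3% and 29.8% with 20, 30 and 50 items. At ICC 0 it stayed near 5%.

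**The case against.** Ordinal regression is not inherently invalid here. A cumulative model can be fitted to one cafeteria percentage with its values kept in order. There is then one row per school, so no clustering; the cafeteria has a baseline percentage to adjust for; and step 4 shows almost no loss of power. This stands, and it means the model cannot be called unusable. It does not rescue the text: the values would not be categorical data as the protocol labels them, and nothing says which of three dependent percentages carries the primary test.

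A reader might infer that the trial will analyse items as independent and so run a type I error of up to 46%. The document does not support that. It never names the item as the unit of analysis, it is silent on a clustering term rather than excluding one, and the figure needs assumed item counts and ICCs.

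A reader might also infer that the score is offered as a second, independent piece of evidence. The protocol says openly that it uses the same frequencies.

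Finally, it is tempting to promote the score to sole confirmatory measure. With analysis already under way, that would be an open invitation to an endpoint-switching criticism. The score is also not equivalent to composition: menus of 50/0/50 and 0/100/0 both score 50.

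The defence that such detail belongs in a fuller plan does not apply to the core point, because the article itself states the data type and the model.

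**Conclusion.** The first primary outcome is misclassified. Its definition gives cafeteria-level percentages; the analysis section calls them ordinal categorical and assigns a model whose response is undefined, while the sample size rests on a comparison of means. That mismatch is certain from the text.

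Its numerical effect is conditional. With many ordered levels of one percentage it is negligible for power. With tertiles it is roughly 8 to 14 points of power at d = 0.5 and about 6 to 7 points at the design effect, where power remains about 90%. With items as the unit and no clustering term, type I error exceeds 5% at every positive ICC tried, but the amount rests on item counts and ICCs that the document does not give. The stated baseline adjustment fails at item level whatever the ICC.

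**What to change.** - Keep menu composition as a primary outcome, and delete the ordinal categorical label.
- Analyse the percentages at cafeteria level as continuous or fractional data, using ANCOVA or the generalized linear model already planned for the continuous outcomes. Adjust for the baseline percentage and for the minimization factors, as the protocol already intends.
- Name one percentage, for example ultraprocessed, as the confirmatory measure. Report the others as adjusted mean differences with 95% confidence intervals.
- Disclose the change and when it was made relative to unblinded analysis.
- Leave the 0 to 100 score secondary, and state that it equals 50 + 0.5 × (%fresh - %ultraprocessed), so that it is not read as independent support.

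The cost is a change of wording, a disclosed late change of model, and the need to choose one percentage. No new data are required, and the stated sample size calculation then matches the type of analysis.

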## Results

This project started receiving funds in early 2018. The educational program was developed in 2018. We administered the intervention program in 2019. All data have already been collected, and we are analyzing the data. In 2020, to ensure ethical and opportunity principles, we offered the educational program to schools from the control group that expressed interest after completion of follow-up. The results are expected in 2021.

## Discussion

This protocol presents a description of the methods to be used to assess the effect of an intervention for the implementation of healthy school cafeterias, ensuring the accuracy of the study and allowing its reproducibility. To our knowledge, this may be the first randomized controlled study in school cafeterias held in Brazil. After the completion of this study, it will be possible to determine whether the proposed educational intervention program is able to improve the menu offered and hygienic conditions of school cafeterias. The results will provide evidence for the formulation of public nutritional and food security policies and for the development of efficacy strategies to provide safe and healthy school meals.

## Appendix

Multimedia Appendix 1 Retrospective questionnaire applied at the end of the intervention program.

Multimedia Appendix 2 Peer review report from the grant agency.
